### Theoretical Framework

Our data collection will be grounded in a behavioral decision research (BDR) approach [40] that will allow us to develop future interventions to inform opioid-related decision-making for patients with metastatic cancer. Opioid-related decision-making refers to decisions to initiate opioids or continue opioids over time. The BDR approach consists of 2 components. The first is the characterization of a “normative decision model,” which describes the information distilled from existing scientific evidence that experts in the field believe that decision makers (patients, care partners, and clinicians) need to know to be able to make an informed decision. The second is a lay “mental model” of the decision, or what interested parties (ie, patients and care partners) already know and how they currently make their decisions. The normative decision model is a well-established approach for medical decision-making [41], including the development of opioid guidelines [42,43]. Consistent with previous studies, the lay decision model solicits perspectives on what patients, care partners, and clinicians consider foundational knowledge and how they make their decisions [44]. Interventions to support optimal decision-making can bridge the gap between the normative model and the contextual reality of how individuals are currently making those choices. Figure 1 provides the BDR framework-based approach mapped to the study aims.

**Figure 1 figure1:**
[figure not shown]
Study aims mapped to behavioral decision-making model element.

### Specific Aims

Using the BDR framework, the objective of this study is to create evidence to guide opioid prescribing in patients with advanced cancer.

The study’s aims are as follows:

Aim 1: To investigate the relationship between opioid therapy and opioid-related benefits.Hypothesis 1a: Prescribed opioids will be associated with decreased pain severity and pain interference (coprimary outcomes).Aim 2: To investigate risk factors for opioid-related harms.Hypothesis 2a: Certain coprescribed medications will be associated with an increased risk of opioid side effects (eg, benzodiazepines and somnolence).Hypothesis 2b: Younger age, history of substance use disorder, and history of mood disorders will be associated with a greater risk of opioid misuse and use disorder.Aim 3: To understand patient, care partners, and clinician perspectives on opioid-related decision-making.

### Study Procedures

#### Recruitment

Potential patient participants will be identified using EMRs; *International Classification of Diseases, Tenth Revision* diagnosis codes; direct clinician referral; and referral from informational handouts in patient-facing platforms (eg, clinic rooms and chemotherapy teach-back packets). Study sites will develop reports to generate lists of potentially eligible patient participants in accordance with all rules of the HIPAA (Health Insurance Portability and Accountability Act), preparatory to the research exception [45]. The research coordinator will review listed patients’ EMRs to verify eligibility following institution-specific procedures for contacting potential patient participants in clinic, over the telephone, or through letters. After receiving permission using one of the methods described above, trained research staff at each site will contact potential patient participants in-clinic or over the telephone to confirm eligibility. Subsequently, research staff will obtain consent, and data will be collected using Research Electronic Data Capture (REDCap; Vanderbilt University), a free and secure web-based application to capture research data [46].

#### Assessments

Once patients have consented and enrolled in the study, data collection will include patient-reported outcomes (PROs), chart reviews, and interviews. Table 1 provides an overview of the study procedures and time frame.

**Table 1 table1:** Schedule of research activities.

Study stage	Screening and enrollment	Follow-up			
	Within 12 weeks of the date of diagnosis	Weekly after baseline	Monthly after baseline	Quarterly after baseline	Semiannually after baseline
Prescreening	✓				
Consent, screening, and contact information	✓				
Demographics and medical history	✓				
Baseline and demographics	✓				
Weekly 3-questions pain assessment: pain severity and inference		✓			
Monthly PRO^a^ assessment: mood, substance use, symptoms, and opioid misuse (Carey 2-year index)			✓		
Chart reviews: substance use, opioid misuse, and opioid overdose				✓	
Patient calls and chart review: Opioid prescription or dose, benzodiazepine prescription, over or under consumption of opioids					✓
TAPS^b^: substance use and opioid use disorder				✓	
Patient participants, care partners, and clinician interviews				✓	

^a^PRO: patient-reported outcome.

^b^TAPS: Tobacco, Alcohol, Prescription Medication, and Other Substance Use Tool.

Study staff will confirm patient demographics and cancer type from the medical record. Sites will use a chart abstraction tool to gather medication-related data every 6 months. Opioid dose will also be assessed through self-report by reading back the dose and instructions on the opioid bottle and confirmed in the EMR. Patient participants will consent to receiving a phone call from the study staff for pill counts during the latter part of the month of their prescriptions every 3 months.

Patient participants will complete baseline assessments and PROs electronically using REDCap, over the phone, or during clinic visits through a tablet by the study staff. If patient participants are unable to complete PROs, care partners will be permitted to complete the PRO assessments on behalf of the patient participants. We acknowledge that based on systematic reviews in oncology, there may be differences in patient-proxy reports, with proxies having a more negative view of the patient’s well-being [47].

The outcome measure for pain will be the Pain, Enjoyment, and General Activity (PEG) scale, a 3-item commonly reliable and validated measure used in oncology populations that asks about pain severity, pain interference in enjoyment of life, and pain interference in general well-being [48-50]. The PEG meets the Initiative on Methods, Measurement, and Pain Assessment in Clinical Trials recommendations and has a 7-day recall period [51]. The PEG will be collected weekly to provide longitudinal impact on pain severity, pain interference, and whether opioids precede any change in pain.

Additional monthly PROs will include information on mood (Functional Assessment of Cancer Therapy-General Well-Being Subscale); comorbidities (Self-Administered Comorbidity Questionnaire); functioning (Carey index); and if prescribed opioids, information on opioid misuse (Patient-Reported Outcomes Measurement Information System), opioid side effects (Patient-Reported Outcomes version of the Common Terminology Criteria for Adverse Events), and substance use (Tobacco, Alcohol, Prescription Medication, and Other Substance Use Tool) [52-56]. These measures were selected because of their favorable psychometrics in the study population, brevity, and similar recall periods. This patient-participant burden is similar to other studies among patients with metastatic cancer [57].

For Aim 3, we will conduct one-on-one interviews with patients, their care partners, and clinicians with the goal of better understanding opioid-related decision-making. These interviews will occur every 3 months for 2 years or until death. The rationale for this frequency is that it strikes a balance between interviewing people often enough for them to remember aspects of opioid decision-making since the last interview but not so often as to ask about opioid-related decisions more frequently than those decisions occur or cause undue participant burden.

### Analytic Plan

#### Aim 1: Data Analysis

This analysis will draw from all patient participants, regardless of whether they are prescribed opioids, so we can compare those who are with those who are not prescribed opioids. We will estimate differences in pain severity and interference between patients treated with opioids versus patients not treated with opioids using linear mixed-effects models, which will allow us to (1) account for repeated measures over time for each patient and (2) adjust for potential confounders. In the linear mixed-effects models, the dependent variables will be based on the PEG: pain severity (first question is a continuous 0-10 value) and pain interference (mean of 3 PEG items) at each time point. Current opioid prescription, baseline pain severity or interference, and other confounders (ie, factors statistically associated with the exposure and outcome) will be included as fixed effects, while the subject will be included as a random effect.

#### Power Calculation for Aim 1

Power calculations were performed by simulation to allow a range of parameters to vary in all scenarios. Unlike a randomized trial, in this study we will not have control over the ratio of patients allocated to the 2 comparison groups (eg, there will not be precisely a 1:1 ratio of patients prescribed opioids vs patients not prescribed opioids for comparison). Scenarios were considered where the proportion of patients prescribed opioids was allowed to vary from 30% up to 70%, all assuming a mean baseline PEG of 6 in the patients not prescribed opioids, a reduction in the PEG of 1 point for patients that are prescribed opioids, and a common standard deviation in PEG scores of 2 points [51]. All scenarios considered had at least 90% power to detect a difference of 1 point between groups with a total sample size of 630 patients (allowing for 30%-70% of the population to be prescribe opioids, meaning that with a range of 189 up to 441 patients prescribed opioids during the study period, there is ample power to detect differences between groups). All scenarios had at least 99% power to detect a 2-point difference on the PEG. We acknowledge that up to 40% of patients may drop out during the study due to the morbidity and mortality of patients in palliative care [58]. Data up until the point of attrition will be included in the analysis, and this has also been accounted for in our calculations.

#### Missing Data for Aim 1

In general, linear mixed-effects models provide unbiased estimates when the data are assumed to be missing at random, meaning that the likelihood of a missing value is not related to the values of the outcome data (in this case, the assumption that missing values for pain are not related to the severity of the patient’s pain). The setting of this study will have two basic missingness problems: (1) data that are missing while the patient still lives, either because the survey could not be completed or the patient did not wish to complete the pain instrument; and (2) pain data that are missing because the patient is deceased. The missing at random assumption can never be fully confirmed, so we will perform three sensitivity analyses to see how our results vary under different approaches to handling the missing pain values: (1) multiple imputations; (2) imputing the worst pain value for patients that fail to complete the pain instrument for any reason (including death before the scheduled assessment); and (3) imputing the worst pain value for patients that fail to complete the pain instrument, but omitting patients that have died. It should be noted that in this patient population, death is an expected outcome and not necessarily a negative outcome with respect to end-of-life suffering and pain management.

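### The coprimary 'pain interference' is scored as the mean of all three PEG items, so it contains the severity item that is the other coprimary

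*Protocol article*

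**What the plan says.** Three places in the protocol article bear on this.

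- **Specific Aims**, Hypothesis 1a, names two outcomes: "Prescribed opioids will be associated with decreased pain severity and pain interference (coprimary outcomes".
- **Assessments** describes the PEG as a three-item scale that "asks about pain severity, pain interference in enjoyment of life, and pain interference in general well-being". That is one severity item and two interference items, all collected weekly.
- **Aim 1: Data Analysis** fixes the scoring of the dependent variables: "pain severity (first question is a continuous 0-10 value) and pain interference (mean of 3 PEG items) at each time point". The fixed effects are listed as "Current opioid prescription, baseline pain severity or interference, and other confounders", so each outcome is adjusted for its own baseline.

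No section gives a two-item interference score or comments on the shared item.

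**The concern.** By the article's own description, the mean of the three items is the overall PEG score. Under the label 'interference' it stands beside its own first item as if the two were separate outcomes.

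The distinction matters here. The Introduction motivates the study with noncancer evidence of a small gain in pain and no gain in function over placebo. Whether interference moves separately from severity is therefore close to the heart of Aim 1. The planned score blurs that question in two ways:

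1. A change in severity alone appears, diluted, as a change in interference.
2. A gain in severity can cancel a real worsening on the two interference items.

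The baseline 'interference' covariate would presumably be scored the same way and carry the same overlap.

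This is not a detail left to a later analysis plan. The article states the scoring, and the statement conflicts with its own description of the instrument.

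**Working it through.** **Inputs from the article (Power Calculation for Aim 1).** Target effect: "a reduction in the PEG of 1 point for patients that are prescribed opioids". Spread: "a common standard deviation in PEG scores of 2 points". Total N = 630, with 30% to 70% prescribed opioids ("with a range of 189 up to 441 patients prescribed opioids during the study period"). Dropout of up to 40%, which if all were lost leaves 630 × 0.6 = 378.

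**Assumptions.** Alpha is not stated, so two-sided 0.05 is used. Each patient contributes one value to a two-group comparison. This simplifies the planned mixed model.

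**Formula.** SE = 2 × √(1/n₁ + 1/n₂); power ≈ Φ(difference/SE − 1.96).

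| N | Split | SE |
|---|---|---|
| 630 | 315:315 | 0.1594 |
| 630 | 189:441 | 0.1739 |
| 378 | 50:50 | 0.2057 |
| 378 | 30:70 | 0.2245 |

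**Step 1: the plan's own figure.** The article states "at least 90% power to detect a difference of 1 point between groups with a total sample size of 630 patients". For a 1-point difference the formula gives at least 0.9999 at N = 630 and 0.994 to 0.998 at N = 378 across the splits. The stated bound is met.

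**Step 2: carry-over.** Let d₁, d₂ and d₃ be the effects on the three items. The planned 'interference' effect is (d₁ + d₂ + d₃)/3. The two-item effect is (d₂ + d₃)/2.

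- Severity only, d₁ = −1, d₂ = d₃ = 0: planned score −0.33, two-item score 0.
- Severity only, d₁ = −2: planned score −0.67, two-item score 0.
- Masking, d₁ = −1, d₂ = d₃ = +0.5: planned score (−1 + 0.5 + 0.5)/3 = 0, two-item score +0.5.

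**Step 3: chance that the severity-only artefact is significant, with SD 2.**

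| Severity effect | Shift in planned score | N = 630, 30:70 to 50:50 | N = 378, 30:70 to 50:50 |
|---|---|---|---|
| 1 point | 0.33 | 0.48 to 0.55 | 0.32 to 0.37 |
| 2 points | 0.67 | 0.97 to 0.99 | 0.84 to 0.90 |

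Example: 0.3333/0.1594 = 2.09, and Φ(2.09 − 1.96) = Φ(0.13) ≈ 0.55. A 70:30 split gives the same values as 30:70. With a two-item score the rejection rate would be alpha, 0.05.

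**Step 4: overlap as correlation.** Assume equal item SDs and a common inter-item correlation ρ (the documents give none). Then corr(item 1, three-item mean) = √((1 + 2ρ)/3), and corr(item 1, mean of items 2 and 3) = ρ/√((1 + ρ)/2).

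| ρ | As scored | Two-item score |
|---|---|---|
| 0 | 0.58 | 0 |
| 0.5 | 0.82 | 0.58 |
| 0.7 | 0.89 | 0.76 |
| 0.9 | 0.97 | 0.92 |

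**Sensitivity to SD.** If 2 is the SD of a single item and ρ = 0.5, the three-item mean has SD 2 × √(2/3) = 1.63. The 1-point artefact is then significant with probability 0.65 to 0.73 at N = 630.

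**The case against.** The scoring mismatch is hard to dispute, but its consequences can be overstated.

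- **A reader might infer that the planned outcomes cannot show a dissociation at all.** That is too strong. From the two estimates, the two-item effect is approximately (3 × composite effect − severity effect)/2. In the severity-only case this is (3 × (−0.333) + 1)/2 = 0. The items are collected, so the information is blurred rather than lost. What stands is that the plan specifies no such recovery as its test, so the coprimary as defined does not answer the question cleanly.
- **The artefact is small on the plan's own scale.** Shifts of 0.33 and 0.67 are below the 1-point target and below the minimum important difference of 1 cited in the Introduction. This stands. Statistical significance is not the same as a claim of worthwhile benefit.
- **The 2-point scenario is extreme.** The only opioid effect on pain that the article quotes is 0.69 (noncancer pain, against placebo). One third is 0.23, which gives 0.26 to 0.30 at N = 630 and 0.18 to 0.20 at N = 378. The N = 378 figures also discard dropouts' data, which the plan keeps. Both points stand, so the probabilities are a conditional worst case.
- **The error is not always towards benefit.** In a nonrandomised cohort, residual confounding that leaves opioid users with higher severity would carry over by the same third, towards harm. This stands.
- **Severity and interference correlate anyway.** That is empirical. The overlap here is arithmetic and present even at ρ = 0.
- **The Assessments section describes the three-item PEG as validated.** That supports using the total. It does not support calling it interference.

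**Conclusion.** The point holds as an error in the definition of a coprimary outcome. One third of any severity effect, in either direction, enters 'interference', and opposite changes on items 2 and 3 can be hidden. The carry-over fraction follows from the scoring alone.

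The rejection probabilities rest on more: exactly no effect on items 2 and 3, SD 2 for the three-item mean, an assumed two-sided alpha of 0.05, and one value per patient.

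Two further inferences are not supported. A reader might expect weekly measurement to raise these probabilities, but that depends on within-patient correlation, changes in exposure and confounder adjustment, none of which the article quantifies. A reader might also conclude that the stated power is wrong. It is not: the bound of 90% is met, and it is no part of this finding. The severity coprimary, the sample size and the data collection are unaffected.

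**What to change.** Define pain severity as PEG item 1 and pain interference as the mean of PEG items 2 and 3. Use the same two-item definition for the baseline covariate in the interference model. If the three-item mean is also reported, label it 'PEG total', not interference.

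Make the change by a dated amendment before the final analysis. Recruitment began in October 2022 and follow-up is due to end by November 2026, so this redefines a coprimary during the study and should be recorded as such.

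No new data are needed, because all three items are already collected weekly. The small downside is that a two-item score departs from the three-item scale that the article describes as validated. Reporting the PEG total alongside it keeps that link.

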### Participants

Patient participants must have an advanced solid cancer diagnosis, defined by the American Cancer Society as cancer that is unlikely to be cured [2]. An advanced cancer diagnosis can include patients who have distant metastases or a recurrence. Patient participants must be their own decision maker as determined by the electronic medical record (EMR) and enroll within 12 weeks of their advanced cancer diagnosis date. The research team will confirm an advanced cancer diagnosis using medical record documentation of pathology results or radiology and oncology documentation. We will recruit patient participants early after diagnosis so that we can understand opioid benefits, harms, and perspectives on opioid decision-making throughout the course of their advanced cancer (up to 2 years). Lived-experience perspectives related to opioid use in those with advanced cancer will be captured by qualitative interviews with a subset of enrolled patients, clinicians, and care partners.

We will specifically elicit information regarding long-term opioid use (ie, opioids for ≥90 consecutive days) and exclude patients on long-term opioid therapy before an advanced cancer diagnosis. Consistent with previous studies, we confirm opioid use in the medical record and will ask patient participants, “Did you take a strong prescription pain medication known as an opioid or narcotic for at least 90 days in a row during the past year? Examples of opioids include oxycodone, hydrocodone, hydromorphone, morphine, fentanyl, buprenorphine, methadone, and combination products such as oxycodone/acetaminophen.” This question is consistent with other commonly used research definitions of long-term or chronic opioid therapy [34,35]. Notably, this long-term opioid use definition also excludes individuals who are receiving methadone or buprenorphine/naloxone (suboxone) for the treatment of opioid use disorder, as the potential benefits and harms of opioid therapy in this population are unique and merit separate investigation [36]. This will allow us to understand the benefits, risk factors for harm, and perspectives on opioid decision-making when a patient with newly diagnosed advanced cancer begins an opioid or continues a newly initiated opioid.

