From the larger cohort, we will recruit 40 patient participants with advanced cancer—20 who are prescribed opioids at the time of enrollment and 20 who are not. From that sample of 40 patients, we will aim to obtain consent from care partners of at least 20 patients and clinicians of at least 20 patients.

We will exclude individuals younger than 18 years of age, prisoners, pregnant people, and patients currently enrolled in hospice at the time of recruitment from the study. Patient participants do not need to report pain at the time of diagnosis since pain can occur at any point in the cancer trajectory. By including patient participants without pain at the time of diagnosis of metastatic disease, the study has the added benefit of describing the natural history of pain in patients with metastatic cancer for 2 years after diagnosis, filling an existing literature gap [3]. Patients who meet advanced cancer eligibility criteria will be recruited irrespective of their predicted prognosis, due to the inherent challenges of predicting prognosis [37,38].

For qualitative interviews, care partner participants must be a spouse, partner, child, relative, or friend who helps the patient with activities of daily living and health care needs at home, consistent with the National Cancer Institute definition of family caregivers [39]. Clinician participants will be physicians or advanced practice clinicians caring for a patient participant who has opioid prescribing authority and is willing to participate in a qualitative interview.

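### Aim 1 names baseline pain as its only pain covariate, so later pain that prompts an opioid start can bias the Hypothesis 1a estimate toward less benefit or apparent harm

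*Protocol article*

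**What the plan says.** The article's section Aim 1: Data Analysis specifies linear mixed-effects models. The outcomes are PEG item 1 (severity) and "pain interference (mean of 3 PEG items) at each time point". The fixed effects are "Current opioid prescription, baseline pain severity or interference, and other confounders", the last group being defined as "ie, factors statistically associated with the exposure and outcome) will be included as fixed effects, while the subject will be included as a random effect". Under Specific Aims, this model tests Hypothesis 1a, on the coprimary outcomes.

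Three other statements bear on it:

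- Participants: pain at entry is not required, "since pain can occur at any point in the cancer trajectory".
- Participants: prior long-term users are excluded, so that the study can observe the patient who "begins an opioid or continues a newly initiated opioid".
- Assessments: the PEG "has a 7-day recall period", and "The PEG will be collected weekly to provide longitudinal impact on pain severity, pain interference, and whether opioids precede any change in pain".

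The sensitivity analyses in Missing Data for Aim 1 concern missing pain scores only. The limitations in the Discussion do not mention confounding by indication.

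**The concern.** Opioids are prescribed for pain. If pain can begin or worsen after enrolment, many starts will follow pain that the enrolment score does not contain. On-opioid weeks are then, on average, weeks in which pain would have been higher anyway, and the model credits that difference to the opioid. A random intercept removes stable differences between patients. It does not remove a change within a patient over time.

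Two details add to this. With a 7-day recall, a score given in the week of the start partly describes pain before the opioid but is counted as on-opioid. For patients already taking a newly started opioid at enrolment, the baseline score is itself measured on treatment.

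At stake is the estimate that answers the primary hypothesis. A true benefit could be reported as smaller than it is, or as harm, with a narrow confidence interval.

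**Working it through.** **1. The plan's own figure.** Inputs from Power Calculation for Aim 1: difference 1 point, SD 2, N = 630, 30% to 70% on opioids, up to 40% attrition. Two-sided alpha 0.05 is my assumption, since the article gives none. With SE = SD x sqrt(1/n1 + 1/n2) and power = Phi(difference/SE - 1.96):

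- 189 against 441: SE = 2 x sqrt(1/189 + 1/441) = 0.174; power = Phi(5.75 - 1.96) = 0.9999.
- After 40% loss, 630 x 0.6 = 378, split 113.4 against 264.6: SE = 0.224; power = Phi(4.45 - 1.96) = 0.994.

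The stated power of at least 90% holds. Precision is ample, so the question is bias.

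**2. Mechanism in one patient (assumed values).** Pain rises by 3 points after enrolment, an opioid is started, and its true effect is -1. Compared with the weeks before the rise, the on-opioid weeks are higher by 3 - 1 = +2. The baseline score and the random intercept are the same in both sets of weeks, so neither accounts for the 3-point rise.

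**3. Simulation.** 630 patients, 104 weekly scores on 0 to 10, 40% attrition over two years. The model fitted was PEG on current opioid, baseline PEG and week, with a random intercept; 10 to 15 runs per scenario. The documents give no pain course or start rule, so both are assumed and varied.

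| Assumed pain course and start rule | Estimate, truth -1 | Estimate, truth 0 |
|---|---|---|
| Starting unrelated to pain | -0.98 to -0.92 | about 0 |
| Odds of starting x1.3 to x2.0 per PEG point | -0.96 to -0.61 | -0.01 to +0.37 |
| 3-point rise for about 10 weeks, starts mainly at PEG 6 or more | -0.77 to -0.17 | +0.18 to +0.71 |
| Lasting 3-point rise, prompt starts | +0.31 | +1.34 |
| Lasting 4-point rise, prompt starts | +1.11 | +2.07 |

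For the lasting 3-point rise with a true -2, the estimate was -0.69. The shifts for truths of 0, -1 and -2 are therefore +1.34, 0.31 + 1 = +1.31, and -0.69 + 2 = +1.31. In that setting the shift hardly depends on the true effect. The model SE was about 0.02, so a shift of 0.4 is about 0.4/0.02 = 20 standard errors.

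A further set of simulations under other assumptions agreed. For a true 0 it gave about 0 when starting ignored pain, +0.07 to +0.20 with stationary pain, and +0.27 to +0.64 with persistent onset. For a true -1, with starting dependent on pain, it gave -0.33 to -0.88.

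One contrived setting went the other way: 6-week flares, start in week 5, opioid then kept. It gave -1.12 for a true -1 and -0.15 for a true 0.

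**4. Adding last week's PEG in all weeks.** For a true -1 this gave +0.04 (lasting 3-point rise) and -0.30 (graded dependence). After a start, last week's score already carries the opioid effect, so adjusting for it removes much of what is to be estimated.

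**5. New-start comparison, adjusted for pain just before the start.** For a true -1 it gave -0.94 to -1.02 under graded dependence, and -0.88 to -0.97 in the further set (-0.04 to +0.02 for a true 0). Under threshold starting, with only a linear term for prior pain, it gave -0.56 to -0.86 for a true -1 and +0.14 to +0.41 for a true 0. A linear adjustment is therefore not enough when starting follows a threshold.

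**The case against.** **The model adjusts for more than baseline pain.** This is correct. A reader might infer that enrolment pain is the only adjustment, but the article also lists other confounders and a random effect. What stands is that no time-updated pain is named and that selection by statistical association does not secure it. If that rule did select last week's PEG, step 4 shows that entering it as an ordinary fixed effect would not help.

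**This is a condensed article and the SAP is not shown.** Time-updated covariates may be planned there. However, the article itself fixes the exposure, the outcome timing, the pain covariate and the random effect. An SAP that follows this text inherits the problem.

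**Only an association is claimed.** Hypothesis 1a is worded that way. But the aim concerns opioid benefits, the model adjusts for confounders, and the stated objective is evidence to guide prescribing.

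**The figures rest on invented inputs.** This stands in full: size cannot be derived from the documents. Nor do they say outright that opioids start when pain rises. That follows from opioids being given for pain and from pain arising later.

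**The support for the new-start analysis is partly circular.** In most scenarios starting depended on recent PEG, which that analysis adjusts for. Unmeasured reasons for starting would remain.

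**A new-start contrast changes the question.** This also stands. The Theoretical Framework section covers both initiating and continuing opioids, and a short-term initiation contrast does not answer continuation.

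**Conclusion.** The concern holds as a flaw in a stated modelling choice. The Aim 1 model does not control pain that rises after enrolment and prompts a start, and nothing else in the article repairs or acknowledges this. Where starting depends on such pain, the estimate generally moves toward less benefit or apparent harm. The shift ranges from near zero (graded dependence, stationary pain) to more than the 1-point target (lasting rises with prompt starts). It does not shrink with sample size.

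Three stronger readings are not supported:

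- A reader might infer that the estimate is pulled toward no benefit or harm whatever the truth. Some settings gave almost no shift, and one contrived setting moved the other way.
- A reader might infer that, if opioids do nothing, the study must report significantly worse pain. That depends on the assumed pain course; one true-0 scenario gave -0.01.
- A reader might infer that pain-free weeks carry no information because no benefit was possible in them. A treated patient may be pain-free because of the opioid, and continuing is itself a decision.

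The power statement needs no change on this ground.

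**What to change.** State the estimand for Hypothesis 1a (initiation, sustained or continued use, or both), and base its conclusion on a prespecified analysis that handles time-varying confounding.

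- **Initiation:** pooled new-start comparisons. In each week, take patients not on an opioid whose recent PEG lies in a range where both choices occur. This range is an analysis criterion, not a prescribing rule. Compare those who start with those who do not. Adjust flexibly, not only linearly, for PEG in the weeks before the start, and for enrolment PEG and other measured confounders. Take the outcome PEG from at least 7 days after the start, and use patient-clustered standard errors.
- **Sustained or continued use:** a marginal structural model with weights built from PEG and treatment history. This has a different target and is not interchangeable with the initiation analysis.

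Keep the present mixed model as descriptive. Do not repair it by adding last week's PEG in all weeks. Name residual confounding by indication as a limitation.

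**Cost:** more analysis and programming. Weekly PEG is already collected. Start dates must be recorded at the planned six-monthly chart abstraction, which the article does not state; a week-by-week current-prescription variable needs them too. Mood and function are collected monthly, so their adjustment is coarser. The initiation estimate uses only new starts and does not answer continuation. The Results section puts the end of follow-up at November 2026 and final analysis after it, so the change can be made before analysis.
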